## Abstract

**Background:**

Chronic obstructive pulmonary disease (COPD) is now one of the top 3 causes of death worldwide. Traditional Chinese medicine (eg, herbal prescriptions and acupuncture), which has a long history of managing respiratory diseases, has shown positive effects in COPD management by alleviating dyspnea, improving lung function, and reducing the risk of acute exacerbations. Patients’ values and preferences are undeniably important in medical decision-making and may affect treatment outcomes and patient adherence.

**Objective:**

This study aims to investigate the preferences for traditional Chinese medicine of patients with COPD, the clinical outcomes they are concerned about, and the trade-offs involved in evaluating the factors that influence treatment selection, such as clinical effectiveness, cost, and adverse effects.

**Methods:**

We will first update previous evidence through a systematic review of randomized controlled trials, examining the efficacy, safety, cost-effectiveness, and patient satisfaction of traditional Chinese medicines for COPD. Subsequently, an exploratory sequential mixed methods study will be conducted comprising qualitative and quantitative components. In this design, qualitative findings are collected first to inform and guide the subsequent quantitative data collection. Semistructured interviews will be conducted to explore in depth the preferences of patients with COPD for traditional Chinese medicine. Insights from these interviews will then be used to design questionnaires that quantitatively investigate the relative importance of different factors influencing patients’ treatment decisions. Data integration will take place by connecting and interpreting the results from both the qualitative and quantitative steps, providing a comprehensive understanding of patient preferences.

**Results:**

This study was approved by the ethics committee of Guangdong Provincial Hospital of Traditional Chinese Medicine on November 6, 2023 (ZM2023-405). A total of 18,188 articles published after 2016 were initially identified in English- and Chinese-language databases. The outline of the semistructured interview guide for this study has been developed. Further clinical evidence updates, qualitative interviews, and discrete choice experiments are still ongoing and will be completed by April 2026.

**Conclusions:**

This mixed methods study might provide important insights into the preferences of patients with COPD for traditional Chinese medicine, assessing trade-offs among efficacy, safety, cost, and other key factors that influence treatment decisions. This study is expected to deepen the understanding of patient-centered decision-making in the treatment of COPD. The findings are anticipated to guide clinical practice, inform policy development, and optimize the integration of traditional Chinese medicine with respiratory care.

**International Registered Report Identifier (IRRID):**

DERR1-10.2196/75426

## Introduction

“Patients’ values and preferences,” as a broad term, is defined as including patient perspectives, beliefs, expectations, and goals for their health and life, including the process that patients go through in weighing the potential benefits, harms, costs, and burdens associated with different treatment or disease management options [1]. Patients’ preferences are based on subjective perceptions and values and are influenced by previous experiences, which may affect treatment outcomes and patient adherence; thus, their importance in medical decision-making is unquestionable [2,3].

Many years ago, patients’ preferences were suggested to be included in clinical practice guidelines [4]. Patient and public representatives are recommended to engage in the guideline development process. On the basis of the requirements of evidence-based medicine (EBM) and narrative medicine, adequate consideration of patients’ needs or understanding of specific treatments is a strong guarantee of scientific and humanized clinical practice guideline development [5]. In addition, understanding patients’ preferences is an important expression of respect for the basic principles of medical ethics [6]. However, patient representatives’ participation [7,8] is insufficient to reflect individual patients’ preferences. Individuals often vary widely in their preferences, even when recommendations are based on rigorous evidence, due to differences in values, experiences, and cultural backgrounds, among other things. Shared decision-making (SDM) is when clinicians and patients participate collaboratively in health decisions after fully discussing treatment options, benefits, and harms, considering the patients’ values, preferences, and circumstances [9]. Applying SDM in clinical practice may result an individualized therapeutic regimen for each patient. Achieving active decision-making requires work by the health care provider and patient. The health care provider teams need to be proactive, and the patient needs to be prepared. Patients increasingly want to be active in clinical decision-making, especially younger patients and those with higher educational levels [10,11]. They want to be informed by their physicians and prefer to learn about their treatment options early and discuss the benefits and drawbacks. Knowing this information can help patients weigh the treatment effects, side effects, and costs so that treatment decisions can be matched to their preferences. Therefore, it remains important for health care providers to recognize patients’ preferences.

Chronic obstructive pulmonary disease (COPD) is a heterogeneous lung condition characterized by chronic respiratory symptoms due to airway or alveoli abnormalities that cause persistent, often progressive, airflow obstruction. COPD is now one of the top 3 causes of death worldwide, and 90% of these deaths occur in low- and middle-income countries [12,13]. It has resulted in a significant economic and social burden that is projected to increase in the coming decades, with substantial morbidity and mortality worldwide [14]. Medication adherence is a major challenge in chronic disease management. A surprising fact is that medication adherence is lower in patients with COPD than in those with other diseases [15], with an average medication adherence of only 60% reported in several studies [16]. Studies have shown that patients with COPD with higher medication adherence have fewer hospitalizations and spend less on treatment compared to those with lower medication adherence [17]. Most of the drugs available for COPD are delivered via inhalers [18,19]. The use of an inhaler requires several steps and differs by device. Patients should receive additional training and education on the use of inhalers, which significantly increases the burden of their disease management [20,21]. Studies indicate that “convenience-related” attributes, such as ease of use, appropriate shape, and low chance of misuse, are among the factors that influence patient preference for inhalers. Furthermore, according to recent work by the World Health Organization and other organizations, inhaled medications are scarcely available and mostly unaffordable for patients with COPD in low- and middle-income countries [22].

Traditional Chinese medicine (TCM) has been used to manage respiratory diseases for thousands of years and has been comprehensively and systematically evaluated for its clinical effectiveness in treating COPD. Evidence shows that TCM therapies, including acupuncture and tai chi, can help improve clinical outcomes such as lung function, quality of life, breathlessness, and exercise capacity in patients with COPD and are safe and reliable [23-25]. Chinese herbal medicines have shown potential benefits for stable or acute exacerbations of COPD [26-28].

The results of a pilot study conducted by our team suggest that the preference of patients with COPD for TCM may be influenced by factors such as clinical efficacy, side effects, and cost [29]. The findings need to be validated in larger samples. In addition, patient perceptions with regard to specific interventions have not been investigated. In this study, we focus on exploring the preferences of patients with COPD during clinical decision-making. *Preference* is defined as patients’ perceptions of TCM for the treatment of COPD, their appraisal of factors for treatment scenarios, and the balance of harms and benefits within or between interventions.

The discrete choice experiment (DCE) is a stated-preference method originating from Lancaster’s economic theory of value and McFadden’s random utility theory, and it has since been widely applied in health care research [30,31]. DCEs can integrate measures of multiple attributes to obtain results closer to real choices, which can adequately predict actual consumer behavior, being generally used in health care preference surveys today [32,33]. There are currently no studies that have used DCE to investigate the preferences of patients with COPD for TCM. Therefore, we will use mixed methods, including both qualitative and quantitative (DCE) methods to obtain more comprehensive information. We hypothesize that clinical practice will be improved by incorporating patients’ preferences. Our objective is to investigate patients’ preferences for TCM for the treatment of COPD; the clinical outcomes they are concerned about; and the trade-offs for the factors of treatment scenario options, such as clinical effectiveness, cost, and side effects. The main research questions are as follows:

What is patients’ perception (such as effect, side effects, and treatment duration) of TCM for COPD?Which clinical outcomes are of most concern for patients, and which factors are important for treatment scenario options?Which factors will influence patients’ options in terms of the available evidence for specific therapies (eg, efficacy, safety, or economic factors)?

## Methods

### Study Design

An exploratory, sequential mixed methods study will be conducted involving a qualitative and quantitative study (DCE) [34]. In an exploratory sequential design, data are first collected and analyzed through qualitative investigation, followed by further exploration of themes derived from the qualitative data via a quantitative investigation. The results from both sets of data are then integrated and interpreted [35]. The attributes of the DCE will be identified from a literature review and the qualitative survey based on previous pilot study results [29]. The results of the qualitative and quantitative study phases will be compared to determine the degree of consistency. This study, which is expected to be completed within 1 year, will be divided into three phases, which are illustrated in the procedural diagram (Figure 1): (1) an update of the existing evidence [23] on the efficacy, safety, economic benefits, and patient satisfaction related to TCM in treating COPD (phase 1; 3 months); (2) a qualitative investigation involving semistructured interviews to explore the perception of COPD, expectations of interventions, and attitudes toward TCM, among other aspects (phase 2; 3 months); and (3) a cross-sectional DCE, which aims to understand participants’ preferences for the TCM interventions and assess the relative importance of different attributes of treatment scenarios through a questionnaire (phase 3; 4 months).

**Figure 1 figure1:**
[figure not shown]
Procedural diagram of the exploratory sequential mixed methods study on patients’ preferences for traditional Chinese medicine in the treatment of chronic obstructive pulmonary disease.

### Participants

Patients aged ≥18 years with a diagnosis of COPD based on The Global Initiative for Chronic Obstructive Lung Disease criteria assessed by a clinical specialist [19] who currently prescribes or has previously prescribed TCM and is able to communicate in Mandarin will be included. Patients with evidence of mental illness, who are judged unable to cooperate or complete the survey, or who are receiving TCM to treat other diseases but not COPD will be excluded. There are no restrictions on the stage and severity of the condition, and a broad range of participants is expected to be enrolled to draw comprehensive conclusions.

Preferences can be diverse in patients from different hospital backgrounds. Recruitment of participants will be conducted based on sufficiently broad background characteristics. Therefore, patients will be recruited from various hospitals. Additional participants will be recruited through newsletters, flyers, or advertisements or when they return for a hospital visit. Participants who have taken part in the interviews will also be invited to take part in the subsequent survey.

All participants will be informed about the study and will sign a consent form before undergoing study procedures.

### Setting

This study will be conducted in a private room at the hospital rather than in the clinic so that patients can relax and openly discuss the interview questions or complete the questionnaires.

### Sample Size

The sample size for the semistructured interviews will be determined through data saturation, and representative participants will be identified using a purposeful sampling strategy. Data saturation will be reached when no additional novel themes emerge from interviews with participants after data analysis and a sufficient number of participants with different characteristics have been interviewed. Between 10 and 20 potential participants will be included in each site considering the diversity of hospitals.

Multiple factors should be considered in the sample size estimation of the DCE survey, such as the heterogeneity of participants, the structure of the DCE questions, the items of the questionnaire, and the expected precision of the results. A sufficiently large sample size is crucial for capturing significant preference changes in the observed population and distinguishing different preferences among subgroups. However, large-scale studies require substantial resources. The thumb formula is a method proposed by Johnson and Orme [36] to calculate the minimum sample size. Considering the limited resources of this study, we used this formula to calculate the minimum sample size required for the DCE main-effects model. In this formula, 500 is a fixed variable, *c* is the maximum number of levels in any attribute, *t* is the number of DCE questions per questionnaire, and *a* refers to the number of options included in each DCE question:

### Data Collection

#### Phase 1

A systematic review will be conducted following the PRISMA (Preferred Reporting Items for Systematic Reviews and Meta-Analyses) guidelines. We will search 3 English-language databases (PubMed, Embase, and Cochrane Library) and 4 Chinese-language databases (Chinese Science and Technology Journal Database, Chinese Biomedical Literature Database, Wanfang, and China National Knowledge Infrastructure) using the following key search terms: “Chronic Obstructive Pulmonary Disease,” “Chinese Medicine,” and “Randomized controlled trials” (more details on the search strategy can be found in Multimedia Appendix 1). Randomized controlled trials exploring the efficacy, safety, and economic benefits of TCM for the treatment of COPD will be included. The initial screening will be carried out independently by 2 researchers who will read the titles, abstracts, and full texts separately and in strict accordance with the inclusion and exclusion criteria. The inclusion and exclusion criteria will be based on a previous systematic review [23]. Data extraction forms will be predesigned using EpiData (version 3.1; EpiData Association), and 2 reviewers will independently extract data from the included studies, checking the data after extraction and resolving disagreements on the extracted data through discussion or third-party assistance.

#### Phase 2

Two researchers will conduct the interviews and collect the data. Both have received training on interviewing techniques and data collection procedures and have experience communicating with patients. To ensure objectivity and minimize potential bias, patient recruitment and scheduling will be handled by a separate research coordinator. The interviewers will not be involved in these preliminary stages and will remain blinded to participant identities until the interviews begin. Before the initiation of the interviews, patients will be briefed on the background and main content of the study and promised that the management of the interview audio recordings will protect their privacy to gain their trust. They will also sign an informed consent form. The open-ended interview questions will be designed by the research team based on a comprehensive review of the literature and findings from our preliminary research (Table 1). The content of the interview outline will be flexibly adjusted according to each individual interview, and the participants will be encouraged to actively express their thoughts in a positive way, choices, and expectations regarding the health care process to obtain richer information from the interviews. Participants can also add any new ideas that are important to them but not covered in the current framework. Basic characteristics (gender, age, educational level, and condition duration) will be collected via a questionnaire. The full interview will be audio recorded, and notes will be taken. The interviews will be conducted in a quiet and private venue to ensure that the interview process is not disturbed and will take 60 minutes on average.

**Table 1 table1:** Topic guide for the semistructured interview used to investigate treatment preferences for traditional Chinese medicine among patients with chronic obstructive pulmonary disease (COPD).

Topic	Relevant questions
Perception of the disease	What are your concerns about COPD and what do you want to know about it? What are your expectations for COPD in the future?
Treatment history	When and under what circumstances did you start receiving traditional Chinese medicine treatment during the course of your illness?
Perception of the treatment	What is your perceived effectiveness of traditional Chinese medicine? Comparing to other treatments you had received throughout the course of illness, what is your perception (such as effect, side effects, and treatment duration) of traditional Chinese medicine for COPD? What clinical outcomes are you more concerned about?
Factors affecting treatment options	Which factors are important for treatment scenario options?

Interviewees will be assigned numbers to protect their privacy, and the audio recordings will be transcribed verbatim by the research team within 24 hours after the interview. Transcripts will be individually coded by the interviewers, and potential themes will be elicited accordingly and then entered into a database (NVivo Plus; version 12; Lumivero). The interviewers will be involved in the coding process and check the coding. Major differences in coding will be discussed and resolved by experienced qualitative researchers.

#### Phase 3

This study’s questionnaire is divided into 3 parts. The first part collects basic personal information of the participants, including age, gender, educational level, primary caregiver, per capita monthly family income, and type of health insurance. The second part focuses on disease and treatment information, such as disease type, stage, and duration and treatment plan. The third part includes preference questions based on identified attributes and levels. Using SAS (version 9.4; SAS Institute), choice sets will be generated via efficient design (*D*–efficiency). When there are too many choice sets, they will be evenly distributed across several questionnaire versions to reduce patients’ burden. Each choice set offers 2 alternatives (options A and B) plus an exit option. To ensure survey quality, the consistency of patients’ pre- and postchoices will be checked by repeating a choice set question and swapping options A and B. Inconsistent choices will be deemed as invalid data.

A pilot survey will be conducted with a small target group to test the comprehensibility of the questionnaire and the rationality of the DCE design. On the basis of this feedback, several discussions will be held to modify and adjust the language and questions of the survey. The same group of participants will then be selected for a second test to gradually improve the reliability and validity of the questionnaire. On the basis of standardized research steps, the research team will strictly control the quality of the questionnaire. The pilot surveys will be completed by the researchers through face-to-face on-site communication to reduce errors and improve the quality of the questionnaire.

Formal research will be carried out in several TCM and Western medicine hospitals. Researchers will distribute and collect paper questionnaires face-to-face to ensure data quality. Before the survey, they will explain the precautions in detail. While patients are filling out the questionnaire, the researchers will answer any questions that arise on the spot.

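### The interview guide invites positively expressed views and asks about starting TCM and its effectiveness, but not about stopping or drawbacks, so drawbacks that mainly interviews would reveal may be under-elicited

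*Protocol article*

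**What the plan says.** The Phase 2 text under Data Collection describes how the semistructured interviews are run. On the interviewers' stance it states that "the participants will be encouraged to actively express their thoughts in a positive way", and the sentence then continues with choices and expectations and gives richer information as the aim. The outline is to be adapted to each interview, and "Participants can also add any new ideas that are important to them but not covered in the current framework".

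Table 1 prints the topic guide. On treatment history it asks "When and under what circumstances did you start receiving traditional Chinese medicine treatment during the course of your illness". On perception of the treatment it asks "What is your perceived effectiveness of traditional Chinese medicine", then, by comparison with other treatments received, "what is your perception (such as effect, side effects, and treatment duration) of traditional Chinese medicine for COPD", then which clinical outcomes concern the patient more. On treatment choice it asks "Which factors are important for treatment scenario options".

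The Participants section makes current or past TCM exposure part of eligibility: "who currently prescribes or has previously prescribed TCM". The Introduction gives as part of the objective the "trade-offs for the factors of treatment scenario options, such as clinical effectiveness, cost, and side effects". Study Design states that the DCE attributes will come from a literature review and the qualitative survey, building on the pilot study.

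**The concern.** An interview phase that feeds a preference experiment should elicit reasons against a treatment as readily as reasons for it. Two features of the printed instrument work against that. The instruction on how participants should express themselves can be taken as a request for favourable views. The guide also asks about the start of TCM and its effectiveness without asking about the opposite side of either.

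Patients who tried TCM and left it are the most direct source on what deters people, and no listed question asks them why they left. A drawback that never surfaces in the interviews, and that no other source supplies, will not become an attribute. It then cannot appear in any choice set or receive any weight in the trade-off. Comparing the qualitative and quantitative phases for consistency cannot be relied on to reveal it, because both would lack it. Each choice set also has an exit option, so information on why patients decline or leave TCM would help in interpreting that option.

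**Working it through.** No arithmetic beyond a count applies; the check is a reading of the instrument against eligibility and against the sources of the attributes.

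**1. Count of questions in Table 1.** Perception of the disease 2, treatment history 1, perception of the treatment 3, factors affecting treatment options 1: 2 + 1 + 3 + 1 = 7.

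**2. What the 7 cover.**
- Starting TCM: 1 question. Pausing or stopping TCM: 0.
- A separate question on effectiveness: 1. A separate question on drawbacks: 0.
- Side effects: named in 1 question, as one of three examples.
- Cost: named in 0, though the open factors question leaves room for it.

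**3. Who can be interviewed.** Read literally, the eligibility sentence attaches the prescribing to the specialist. The treatment-history question presupposes that every interviewee has had TCM, so the sensible reading is that patients with current or past TCM prescriptions qualify. On that reading people who have stopped can be in the sample. No number or quota of past users is given.

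**4. Which sources can supply each kind of drawback.**

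| Drawback | Pilot study | Phase 1 review | Interviews |
|---|---|---|---|
| Side effects | Named | Safety is covered | Named as an example |
| Cost | Named | Economic benefits are covered | Open factors question only |
| Reasons for stopping, burden, inconvenience | Not named | Not a stated topic; review is of randomized trials | No direct question |

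Patient satisfaction is also within the review's stated scope and could touch on the third row, but trial reports are an indirect source for why patients stop TCM in ordinary care. The third row therefore depends mainly on the interviews, and there the guide has no direct question.

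**5. The instruction.** If the disputed phrase describes manner (being forthcoming), it adds little to the adverb that precedes it. If it describes content, it is leading. The text does not settle which, and two interviewers work from it.

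**The case against.** The case on the other side is substantial.

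- *The phrase may describe manner.* It sits in a garbled list, and the stated aim is richer information. This stands: the favourable-content reading is possible, not proven.
- *The guide is not uniformly one-sided.* The question on concerns about COPD, the comparison with other treatments, the question on outcomes and the factors question are all reasonably neutral, and the comparison names side effects. This stands, so it would be wrong to say that the instrument as a whole steers patients.
- *Interviews are flexible, and participants may add topics.* This lowers the risk. It leaves drawbacks to the patient's initiative and the interviewer's discretion, whereas effectiveness is a listed topic.
- *The article is condensed, and a fuller guide may hold follow-up probes.* It may, so one cannot say that stopping will never be discussed. But Table 1 is printed as the topic guide and the Results section reports its outline as developed, so its wording can fairly be judged.
- *Findings are returned to some participants, and the DCE questionnaire is piloted.* Both help, but the first checks what was said and the second tests comprehensibility and design. Neither is aimed at finding omitted drawbacks.

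A reader might infer that the DCE attributes will under-represent drawbacks in general, and cost in particular because no question names it. The document does not support that. Study Design draws the attributes from the literature review and the pilot as well as the interviews. The pilot already identified side effects and cost, and the review covers safety and economic benefits.

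**Conclusion.** The point holds in a limited form. The instruction on positive expression is ambiguous and can be read as leading. The printed guide has 0 of 7 questions on pausing or stopping TCM and 0 of 7 on drawbacks as such, against one on starting and one on effectiveness. This creates a risk, not a certainty, that drawbacks which mainly interviews would reveal are under-elicited in the qualitative input to the DCE. Side effects and cost are less exposed.

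The effect cannot be quantified: the share of past users among interviewees is not stated, and how interviewers will apply the instruction is unknown. The conclusion assumes that past TCM users are eligible as patients and that Table 1 reflects what interviewers will ask. It is a low-cost improvement to a stated instrument; it does not invalidate the design.

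**What to change.** Three wording changes:

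1. In the Phase 2 text, replace the phrase on positive expression with a neutral instruction that interviewers invite favourable and unfavourable views equally.
2. In Table 1, extend the treatment-history question to ask whether TCM was ever paused or stopped and, if so, why.
3. In Table 1, pair the effectiveness question with one on what the patient has found to be the drawbacks of TCM.

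The cost is a revised guide and a short briefing for the two interviewers; interviews, now averaging a planned 60 minutes, may run a few minutes longer. The Results section reports the interviews as still ongoing, so the change is worth most if made before they finish and the attributes are fixed. Naming cost as a prompt, changing the question order or imposing a uniform probe list is optional; the point does not depend on any of these.
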